### Analysis of primary outcome

The primary analysis will be conducted on the FAS and PPS, which is the rate of self-reported clinical symptoms, including fever, fatigue, and coughing recovery. The percentage of patients whose clinical symptoms disappeared on the seventh day will be summarized. CMH-Chisquare test will be applied to compare rates between groups and Clopper-Pearson method will be used to calculate the 95%CI for rate difference (Table 3).

**Table 3 T3:** Analysis of the primary outcome.

	Full analysis set				Per Protocol set			
Variables	SHHS group (n=xx)	LHQW Group (n=xx)	Rate difference 95%CI	*P-Value*	SHHS group (n=xx)	LHQW Group (n=xx)	Rate difference 95%CI	*P-Value*
Rate of clinical symptom recovery at days 7 (n,%)^b^	xx (xx%)	xx (xx%)	xx%(xx% to xx%)	.xx	xx (xx%)	xx (xx%)	xx%(xx% to xx%)	.xx

b Number, percentage.

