### Sample size

The study hypothesis is SHHS group will be non-inferior to LHQW group. Clinicians and statisticians set the non-inferiority threshold at 10% and predicted that the recovery rate of clinical symptoms after 7 days of LHQW is about 87% and that of SHHS is 90% according to the literature reports on similar drugs. It is estimated that 94 patients for each group, ie. a total of 188 patients are needed to achieve the power of 80% at a one-sided statistically significant level of 0.025. Considering the possible dropout rate of 20%, 240 patients will be enrolled, that is 120 patients for each group.

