## Statistical analysis plan

### Statistical methods

The statistical analysis plan will comply with the guidelines for the content of statistical analysis plans in clinical trials (Gamble et al., 2017). (**Additional File 3**). After finishing the trial, all statistical analysis tests will be conducted using SAS (version 9.4; SAS Inc., Cary, NC, USA) and one-sided tests with a nominal alpha level of 0.025. All confidence intervals (Cls) will be stated at the 95 confidence level. To assess non-inferiority, the CI lower limit of the difference between groups will be compared with a predefined non-inferiority limit. Non-inferiority could only be declared when the 95% CI lower limit of the difference between groups is not larger than the non-inferiority threshold of 10%.

Continuous outcomes will be described by calculating the mean, standard deviation, median, and minimum and maximum values. The means and standard deviations are reported for normal continuous data. For non-normally distributed continuous variables, the median and interquartile ranges are given. The frequency and proportion of each category are displayed as counting indications.

Between-group comparisons are performed using an independent two-sample t-test (normality, homogeneity of variance) or the Wilcoxon rank-sum test (non-normality, heterogeneity of variance). The paired t-test is used for comparisons within normally distributed groups, and the paired rank-sum test is used for comparisons within non-normally distributed groups. For count metrics, the χ^2^ test or Fisher's exact probability will be required, whereas, for categorical variables, the Wilcoxon rank-sum test will be utilized. Repeated measured outcomes are applied to a generalized linear mixed model analysis.

In patients where baseline indicators are unbalanced, an adjustment to the efficacy contrast of variables such as age, sex, and concurrent therapy is required. The covariance approach is employed for continuous variables, and for count or rank data, logistic regression analysis is performed.

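### Clopper-Pearson, the interval method named for the primary rate difference, covers one proportion only, so it cannot supply the lower limit that decides non-inferiority

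*Protocol article*

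**What the plan says.** The Sample size section sets the hypothesis: "The study hypothesis is SHHS group will be non-inferior to LHQW group". It uses a margin of 10% and assumed recovery rates of 87% (LHQW) and 90% (SHHS), with "power of 80% at a one-sided statistically significant level of 0.025". The result is 94 evaluable patients per arm and 120 per arm enrolled.

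The Statistical methods section specifies "one-sided tests with a nominal alpha level of 0.025" and 95% confidence intervals. It bases the non-inferiority decision on comparing the lower end of the interval for the between-arm difference with the margin.

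For the primary outcome, the Analysis of primary outcome section names the methods: "CMH-Chisquare test will be applied to compare rates between groups and Clopper-Pearson method will be used to calculate the 95%CI for rate difference". Table 3 shows the rate difference with its 95% interval and one P value without a label, for the full analysis set and for the per-protocol set. The article names no other interval method for this difference and no test against the margin.

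**The concern.** Clopper-Pearson inverts the binomial test for one proportion. With two arms it yields two separate intervals, one per recovery rate. It has no version for the difference of two independent rates, and that difference is what the decision rule needs.

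The plan therefore has a suitable kind of rule but no working method to feed it. The analyst must choose a substitute, possibly after the data exist and in an open-label trial. Plausible substitutes can disagree on the same data about whether non-inferiority is shown, and they differ widely in power.

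A smaller mismatch sits beside it. The only test named, the CMH chi-square, addresses a difference of zero, whereas the hypothesis is about a margin of 10 points.

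**Working it through.** **Inputs.** From Sample size: LHQW 0.87, SHHS 0.90, margin 0.10, one-sided 0.025, power 80%, 94 per arm evaluable, 20% dropout, 120 per arm enrolled. The margin is printed without a sign. I read it as SHHS minus LHQW above -10 percentage points.

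**The plan's own figure.** With unpooled variance:

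n = [0.87×0.13 + 0.90×0.10] × (1.960 + 0.842)² / (0.03 + 0.10)² = 0.2031 × 7.849 / 0.0169 = 94.3 per arm.

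The plan states 94, where rounding up would give 95. Power at 94 is Φ(0.13/√(0.2031/94) − 1.960) = 79.9%. For dropout, 188/0.8 = 235, rounded up in the plan to 240. The sample size therefore reproduces, and it does so with a 10-point absolute margin on the lower side.

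**What the named method gives.** Take 85/94 (SHHS) against 82/94 (LHQW), close to the planning rates. Clopper-Pearson gives 82.6% to 95.5% and 78.8% to 93.2%. It gives nothing for the difference of 3.2 points. Possible substitutes on these data:

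- SHHS lower limit minus LHQW upper limit: 82.6 − 93.2 = -10.6 points, so non-inferiority fails.
- Newcombe: -6.1 points, met.
- Wald: -5.8 points, met.

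With 104/120 in both arms, the subtracted limits give -12.9 points (fails) and Newcombe gives -8.8 (met). The substitutes do not always disagree: at 108/120 against 104/120, subtraction gives -9.0 and Newcombe -5.0, and both meet the margin.

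**Operating characteristics.** These come from exact enumeration of both binomials, with success declared when the lower limit of the two-sided 95% interval exceeds -10 points. Power is at 90% against 87%. Error is at the margin, 77% against 87%.

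| Method | Power, 94 per arm | Power, 120 per arm | One-sided error (94; 120) |
|---|---|---|---|
| Wald | 80.0% | 88.7% | 2.7%; 2.7% |
| Newcombe | 78.0% | 87.2% | 2.6%; 2.6% |
| Miettinen-Nurminen | 77.8% | 87.2% | 2.4%; 2.5% |
| Subtracted Clopper-Pearson limits | 42.9% | 59.3% | 0.2%; 0.2% |

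If the name was meant loosely for some exact procedure for two proportions, the choice still matters. An exact unconditional test ordered by the score statistic has power of about 77% and 87%. One ordered by the raw difference has about 35% and 51%.

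**The P value.** A chi-square test of equality does not follow the non-inferiority conclusion:

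- 104/120 in both arms: P = 1.00, Newcombe lower limit -8.8 points (met). One-sided P against -10 points (Farrington-Manning) = 0.014.
- 100/120 against 104/120: P = 0.47, Newcombe lower limit -12.5 points (not met). One-sided P against -10 points = 0.077.

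At the planning rates the equality test is significant in only 9.9% of trials at 94 per arm and 11.1% at 120.

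**The case against.** The strongest defence is that the framework is sound. The decision rests on a confidence limit for the rate difference, the 95% level matches one-sided 0.025, and the sample size fits a 10-point margin. On this view only a method name is wrong, and a competent analyst would use a proper difference interval. Most of this stands, and it limits the point to the interval. It does not remove the point, because the article names a method and that method does not apply. An analysis plan that is not shown could not make the sentence correct.

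Three stronger readings are tempting, and the document supports none of them.

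- **The trial cannot test non-inferiority.** The Statistical methods section already contains a rule of the right type. What is missing is a valid interval to put into it.
- **The trial has 43% power.** Nowhere does the article say that single-arm limits will be subtracted. The 43% and 59% describe one possible substitute, and its error of 0.2% means that it risks missing non-inferiority, not claiming it falsely.
- **The CMH P value decides, so P above 0.05 would pass as non-inferior.** The Statistical methods section allows the claim only through the confidence limit. The P value is a reporting mismatch.

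That no CMH stratum is named is detail a condensed article may leave out, and I make nothing of it.

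**Conclusion.** The point holds for the interval. The method named for the primary rate difference cannot produce the number on which the primary conclusion depends. Across the substitutes examined, power at 94 per arm runs from about 35% to 80%, and on the same plausible data the verdict can go either way. Only an established interval for a difference, or an exact test ordered by the score statistic, comes near the stated 80%.

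This rests on the planning rates of 87% and 90%, on independent binomial arms, and on reading the margin as -10 percentage points, which the plan's own sample size supports. The CMH P value is a secondary labelling matter. Because the interval governs the primary conclusion, it must be corrected before the database is locked.

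**What to change.** In Analysis of primary outcome, replace Clopper-Pearson with one named interval for the difference SHHS minus LHQW: Miettinen-Nurminen or Newcombe score, two-sided 95%. State that non-inferiority is declared only if its lower limit lies above -10 percentage points. Align the rule in Statistical methods with this, since it prints the threshold without a sign and words the direction of the comparison the wrong way round. Stratifying the interval is optional and would need prespecified strata; Randomization and allocation names no stratification factor.

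In Table 3, either replace the P value with a one-sided non-inferiority P value against -10 points (Farrington-Manning) or label it as a supportive test of equality.

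The cost is a few sentences and a few lines of analysis code. No further data or patients are needed, and the sample size stays as planned: with a valid interval, power is about 78 to 80% at 94 per arm and 87 to 89% at 120.

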### Recruitment of participants

This study will include 240 patients who test positive for COVID-19. The patients will be recruited from the Affiliated Hospital of Changchun University of Traditional Chinese Medicine (Jilin province, China). Recruiting advertising will be displayed online and on hospital notice boards. It will contain the study objectives, drugs, medical examinations, and the study eligibility conditions and application method. The study is open to individuals who meet the eligibility criteria and agree to participate. To obtain consent from prospective patients, investigators must outline the study objectives, requirements, and interventions and guarantee their understanding. Two resident physicians will evaluate the patients, each of whom will verify the participants’ study eligibility. Demographic data and reasons for non-participation of ineligible patients will also be documented. The recruitment process started in March 2022 and will last until March 2024. Patients will not participate in study design, recruitment, research procedures, analysis, or dissemination of findings. Medical examinations, laboratory tests, and therapies are provided at no cost to participants, and research may not reimburse them.

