### Inclusion criteria

Diagnostic criteria for COVID-19 are based on the Protocol for the Diagnosis and Treatment of Novel Coronavirus Disease 2019 (9th edition) released by the NHC of the People's Republic of China (General Office Of The National Health And Health Commission, 2022) and include individuals who qualified for eligibility meeting the following criteria: 1) clinically confirmed patients of COVID-19 according to the Protocol for Diagnosis and Treatment of Novel Coronavirus Pneumonia (9th edition) with laboratory confirmed SARS-CoV-2 infection as determined by RT-PCR; 2) patients judged to have mild or moderate COVID-19. (Patients with mild COVID-19 usually present with mild clinical symptoms, without radiological manifestations of pneumonia, whereas patients with moderate COVID-19 patients have a fever and respiratory symptoms, as well as radiological features of pneumonia); 3) presence of one or more symptoms of fever, cough, sore throat, and fatigue when entering the group; 4) the time of admission is not more than 24 hours; 5) patients of either sex who are 18 years or older, and 6) providing written informed consent before enrolling in the trial.

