### Randomization and allocation

A permuted block randomization procedure will be used to allocate 240 eligible patients in a 1:1 ratio. Randomization numbers will be generated using the PROC PLAN process statement in the SAS statistical software package (version 9.4; SAS Inc., Cary, NC, USA). Patients will be assigned to either the SHHS or LHQW group. The Department of Statistics at the Nanjing Medical University will be responsible for randomization. Randomization code will be concealed in opaque envelopes and the allocation information will not be known before randomization procedure.

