### Descriptive statistics

Participants' baseline characteristics will be reported in a baseline table for each randomization group, and baseline data and descriptive statistics will be assessed using standard measures in accordance with the recommendations of the consolidated standards of reporting trials (CONSORT) guidelines (Moher et al., 2010). (Table 2). The table describes the following variables: age, sex, height, weight, clinical symptoms, and medical and treatment histories. The sample is displayed in accordance with the entire analysis set. Baseline characteristics will be compared between the groups.

**Table 2 T2:** Baseline demographic and clinical characteristics.

Variables	SHHS Group (n=xx)	LHQW Group (n=xx)	All participants (n=xx)	*P-value*
Age (year)^a^	xx (xx)	xx (xx)	xx (xx)	.xx
18≤Age<65	xx (xx)	xx (xx)	xx (xx)	.xx
Age≥65	xx (xx)	xx (xx)	xx (xx)	.xx
Males sex^b^	xx (xx%)	xx (xx%)	xx (xx%)	.xx
Height (cm)^a^	xx (xx)	xx (xx)	xx (xx)	.xx
Weight (kg)^a^	xx (xx)	xx (xx)	xx (xx)	.xx
Vital signs				
Heart rate (beats/minute)^a^	xx (xx)	xx (xx)	xx (xx)	.xx
Respiratory rate (breathe / minute) a	xx (xx)	xx (xx)	xx (xx)	.xx
Pulse Rate (beats/minute)^a^	xx (xx)	xx (xx)	xx (xx)	.xx
Systolic blood pressure (mmHg)^a^	xx (xx)	xx (xx)	xx (xx)	.xx
Diastolic blood pressure (mmHg)^a^	xx (xx)	xx (xx)	xx (xx)	.xx
Temperature (°C)^a^	xx (xx)	xx (xx)	xx (xx)	.xx
Past medical history^b^	xx (xx%)	xx (xx%)	xx (xx%)	.xx
Diabetes^b^	xx (xx%)	xx (xx%)	xx (xx%)	.xx
High blood pressure^b^	xx (xx%)	xx (xx%)	xx (xx%)	.xx
Coronary artery disease^b^	xx (xx%)	xx (xx%)	xx (xx%)	.xx
Chronic obstructive pulmonary disease^b^	xx (xx%)	xx (xx%)	xx (xx%)	.xx
Stroke^b^	xx (xx%)	xx (xx%)	xx (xx%)	.xx
Cancer^b^	xx (xx%)	xx (xx%)	xx (xx%)	.xx
Heart failure^b^	xx (xx%)	xx (xx%)	xx (xx%)	.xx
···	···	···	···	···
Disease diagnosis^b^	xx (xx%)	xx (xx%)	xx (xx%)	.xx
Mild^b^	xx (xx%)	xx (xx%)	xx (xx%)	.xx
Moderate^b^	xx (xx%)	xx (xx%)	xx (xx%)	.xx
Initial symptoms^b^				
Fever^b^	xx (xx%)	xx (xx%)	xx (xx%)	.xx
Cough^b^	xx (xx%)	xx (xx%)	xx (xx%)	.xx
Fatigue^b^	xx (xx%)	xx (xx%)	xx (xx%)	.xx
Diarrhea^b^	xx (xx%)	xx (xx%)	xx (xx%)	.xx
Shortness of breath^b^	xx (xx%)	xx (xx%)	xx (xx%)	.xx
Sore throat^b^	xx (xx%)	xx (xx%)	xx (xx%)	.xx
Nausea^b^	xx (xx%)	xx (xx%)	xx (xx%)	.xx
Vomiting^b^	xx (xx%)	xx (xx%)	xx (xx%)	.xx
Taste and smell dysfunction^b^	xx (xx%)	xx (xx%)	xx (xx%)	.xx
Loss of appetite^b^	xx (xx%)	xx (xx%)	xx (xx%)	.xx
···	···	···	···	···

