## Discussion

The ongoing COVID-19 pandemic, which has been spreading for more than two years, has led to various variants of SARS-CoV-2 (Tao et al., 2021; Khandia et al., 2022). The increased transmissibility or severity of SARS-CoV-2 continually poses serious challenges to vaccine development and targeted therapeutic strategies (Dong et al., 2021; Lino et al., 2022). Timely intervention with TCM in COVID-19 has been shown to significantly relieve symptoms, shorten the course, and improve the prognosis of the disease An et al., 2021. The trial is a randomized, active-drug parallel-controlled, open-label, non-inferiority clinical trial carried out in China to evaluate the effectiveness of SHHS compared to LHQW among patients with COVID-19. This phase 2 clinical trial will provide clinical evidence of TCM herbal preparations for preventing and treating COVID-19. The SAP was developed to prepare for statistical analysis of all data after the completion of this study and locking of the database. Although this is a single-center and open-label study, the quality of evidence will be improved by strict quality control and transparent reporting. The findings of this study will have important implications both for Chinese and western clinical practices. Furthermore, if the non-inferior conclusion could be declared in our study, SHHS granules will be confirmed its effects not only for symptoms management of COVID-19 and reducing the severe incidence, but also for extended indications of virus pneumonia or influenza. All of these depend on integrated multi-source high-quality data including randomized controlled trials and observational studies in the future.

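### The primary CMH test names no stratification factor, so as written it is an ordinary chi-square, and the rate-difference interval that decides non-inferiority uses no baseline information

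*Protocol article*

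**What the plan says.** All references are to the protocol article.

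- **Test.** Under *Analysis of primary outcome*, "CMH-Chisquare test will be applied to compare rates between groups". No stratification factor is given.
- **Interval.** The same section says that "Clopper-Pearson method will be used to calculate the 95%CI for rate difference", again with no covariate or stratum.
- **Decision rule.** Under *Statistical methods*, "the CI lower limit of the difference between groups will be compared with a predefined non-inferiority limit". The interval decides non-inferiority; the CMH p-value does not.
- **Randomisation and sites.** "A permuted block randomization procedure will be used to allocate 240 eligible patients in a 1:1 ratio", with no stratification factor named. Recruitment is at one hospital (*Recruitment of participants*), and the *Discussion* begins a sentence with "Although this is a single-center and open-label study".
- **Population.** *Inclusion criteria* admit both mild and moderate disease and require "presence of one or more symptoms of fever, cough, sore throat, and fatigue when entering the group". A patient may therefore enter with one to four of these symptoms. *Secondary outcomes* defines recovery as the main symptoms having disappeared.
- **Baseline data.** Table 2 has rows for mild and moderate diagnosis and for each initial symptom. Severity is recorded directly, and a symptom count can be derived.
- **Adjustment.** *Statistical methods* calls for adjustment where baseline indicators turn out unbalanced. It gives age, sex and concomitant treatment as examples, and logistic regression as the method for count data.
- **CMH elsewhere.** For secondary outcomes, a chi-square or Fisher test compares the groups, and CMH appears separately as a way to examine covariates.

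**The concern.** The article itself uses CMH as a covariate tool for the secondary outcomes. For the primary outcome it names the method without the input that distinguishes it from a chi-square. As written, the name suggests an adjustment that does not take place.

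The larger matter is the interval. A patient who enters with four symptoms has more to clear by day 7 than one who enters with one, and moderate disease includes radiological pneumonia. It is reasonable to expect both factors to be related to recovery. Both are available at baseline, yet the quantity compared with the 10-point margin uses neither.

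The imbalance rule does not fill the gap. It operates only after baseline data have been seen, its list of variables is open-ended, and it names neither severity nor symptom burden. For a binary outcome it leads to an odds ratio, on a different scale from the margin. What is at stake is some precision, and a primary estimate whose adjustment is not settled in advance.

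**Working it through.** **1. The plan's sample size.** Inputs from *Sample size*: LHQW 87%, SHHS 90%, margin 10 points, one-sided alpha 0.025, power 80%.

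- Variance term: V = 0.90×0.10 + 0.87×0.13 = 0.2031.
- Distance to the margin: 0.90 - 0.87 + 0.10 = 0.13.
- n per arm = (1.960 + 0.842)² × 0.2031 / 0.13² = 94.3. The article states 94, so its figure is reproduced to within rounding.
- Power at 94 per arm = Φ(0.13/√(0.2031/94) - 1.960) = 79.9%. This is the reference below.

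**2. CMH with one stratum.** The CMH statistic uses the hypergeometric variance, with N-1 where Pearson's has N, so CMH = Pearson × (N-1)/N.

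| Illustrative result | Pearson (p) | CMH (p) | Ratio |
|---|---|---|---|
| 108/120 vs 104/120 | 0.6469 (0.421) | 0.6442 (0.422) | 239/240 = 0.9958 |
| 86/96 vs 84/96 | 0.2053 (0.650) | 0.2043 (0.651) | 191/192 = 0.9948 |

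Without strata the two tests are the same for practical purposes.

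**3. What a stratified risk difference would gain.** The documents give no recovery rates by severity or symptom count, so the gap g between strata and the share s of patients in the worse stratum are assumptions. Overall rates stay at 87% and 90%. The between-stratum variance removed is 2s(1-s)g², and the fraction removed is 2s(1-s)g²/0.2031. Example with s = 0.3 and g = 0.15: 2×0.21×0.0225/0.2031 = 4.65%. In each cell below, the first value is for s = 0.3 and the second for s = 0.5.

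| Gap g | Variance removed | n per arm for 80% power | Power at 94 per arm |
|---|---|---|---|
| 5 points | 0.5% / 0.6% | 93.8 / 93.7 | 80.1% / 80.1% |
| 10 points | 2.1% / 2.5% | 92.4 / 92.0 | 80.7% / 80.8% |
| 15 points | 4.7% / 5.5% | 89.9 / 89.1 | 81.7% / 82.1% |
| 20 points | 8.3% / 9.9% | 86.5 / 85.0 | 83.2% / 83.8% |

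If all 120 per arm are analysed, the same formula gives 88.5% power unadjusted and between 88.6% (g = 5, s = 0.3) and 91.4% (g = 20, s = 0.5) stratified. The 95% half-width, 1.960×√(V/120), goes from 8.06 points to between 8.04 and 7.66.

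**4. Chance imbalance.** Assume 30% moderate patients and a mild-moderate gap of 13.5 points. The SD of the between-arm difference in the moderate share is √(2×0.3×0.7/120) = 5.9 points. A one-SD imbalance moves the unadjusted rate difference by 0.059×13.5 = 0.8 points.

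**The case against.** **The test is valid and decides nothing.** This is correct. A one-stratum CMH test is a sound chi-square, and the interval settles non-inferiority. Adding strata to the p-value alone would not change the conclusion, which is why the fix has to reach the estimate and its interval.

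**Strata may be named in a fuller plan.** This also stands. A reader might infer that no strata exist, but the article supports only that none is named. CMH strata need not be randomisation factors. Even so, the article presents these sections as its predetermined analysis plan, gives an incomplete primary method there, and fixes a different, imbalance-triggered route to adjustment.

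**Imbalance is already handled.** Only in part. The listed variables are examples, so severity could be added, and Table 2 compares it between arms. The rule still depends on the observed data and does not give a rate difference to set against the margin.

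**The gain is small and assumed.** This stands. A reader might take severity and symptom count to be strong predictors, but no figure in the documents shows it. At a 5-point gap the benefit is negligible. The two factors are also linked, since the inclusion criteria describe moderate patients as having fever and respiratory symptoms; using both may add less than two independent factors would.

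**Chance imbalance is not bias.** A reader might infer that the unadjusted comparison is distorted. It is not: the 0.8-point shift is ordinary sampling variation already reflected in the unadjusted interval, and largely the same loss as the variance in step 3. A shift above one point would need a gap above 1/0.059, about 17 points.

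**Conclusion.** The point holds as a low-cost improvement, not as an error that invalidates the analysis. On the text shown, the primary CMH test has no stratification factor and is in practice a chi-square. The interval that decides non-inferiority is unadjusted, and the only adjustment rule is triggered by the data and does not yield a rate difference.

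The gain from prespecified stratification is about 0.5% to 10% of the variance, or roughly 0.2 to 3.9 points of power at 94 per arm. This assumes stratum gaps of 5 to 20 points, 30% or 50% of patients in the worse stratum, overall rates as planned, and balanced strata. If analysed numbers approach 120 per arm, power is already 88.5% and the gain is about 0.1 to 2.9 points. Settling the primary estimate before the data are seen has value whatever the size of the gap.

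**What to change.** Before database lock:

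1. Name the strata: baseline mild/moderate severity and a baseline symptom-count category based on the four entry symptoms. The cut (for example 1-2 versus 3-4) is not given by the documents. It can be chosen from cell sizes pooled over arms.
2. Make the primary estimate the Mantel-Haenszel stratified risk difference, SHHS minus LHQW, or a risk difference standardised from a logistic model with the same factors. Give it a matching 95% CI, use it whatever the observed balance, and compare its lower limit with -10 points.
3. Report the unstratified difference with its interval as a sensitivity analysis.
4. State that this replaces the imbalance-triggered rule for the primary outcome.
5. If a test is reported beside the interval, use the same strata in the CMH test. If the sponsor prefers no strata, call it a plain chi-square.

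The cost is a few sentences in the analysis plan. Both factors come from data already planned for Table 2, so no new data, visits or patients are needed.
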